### Sample size

Sample size for the pilot trial is calculated to recruit at least 30 participants in each arm in order to estimate the pooled standard deviation of the outcome with a reasonable degree of precision for the full trial [48, 49]. We have estimated that attrition will be 20% based on a preliminary feasibility-controlled case series [50] and that a further 20% joining the STAR cohort will either not meet the first trial inclusion criteria or not accept the offer of treatment.

Sample size for the full trial will be based upon results obtained in the pilot. The calculation will be based upon the obtained effect size (SMD) for the primary outcome, significance (alpha error) of 0.05 and power of 80% and adjusted according to the levels of attrition observed. If an effect size of .4 is obtained in the pilot, then the outcomes of approximately 100 participants per group will be required. If estimated attrition of 40% is correct, then 166 participants per group will need to be recruited to the cohort.

Participants are recruited from registered charities, schools, word of mouth and support groups. The majority of participants are recruited from the city of Sheffield; however, participants are also recruited nationally and the feasibility of on-line treatments assessed.

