### Inclusion/exclusion criteria

Inclusion criteria for the STAR cohort are children aged 5–18 (inclusive) with a carer-reported diagnosis of ADHD (date, venue and diagnosing physician) and a carer-reported Conners Global Index (CGI) *T* score of at least 55 (denoting mild atypicality (Table 1). Inclusion criteria for the trial are a carer-reported CGI score of at least 65 (indicating a significant problem) (Table 1).

**Table 1 Tab1:** Interpretive guideline for Conners’ *T* scores and percentiles

*T* score	Percentile	Guideline
70+	98+	Markedly atypical (significant problem)
66–70	95–98	Moderately atypical (significant problem)
61–65	86–94	Mildly atypical (possible problem)
56–60	74–85	Slightly atypical (borderline)
< 30–55	< 2–73	Average (typical: should not raise concern)

Exclusion criteria to both cohort and trial are children below the age of 5 or adults over 18; children with terminal, severe, life-limiting conditions; and families where English is not written or spoken (as the project does not have funds to provide a translation service). Exclusion criteria to the trial are children currently receiving treatment by a homoeopath or a nutritional therapist and children with CGI *T* scores below 65.

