### Outcome measurement

Carers of children with ADHD are asked to complete carer questionnaires (CQs) sent to them by post or completed on-line (www.starsheffield.com).The CQ includes the 10-item Conners’ Global Index (CGI) [47]; the 18-item Swanson, Nolan and Pelham Teacher and Parent Rating Scale (SNAP) [51]; the 9-item Child Health Utility health-related quality of life (CHU-9) measure [52]; and questions about resource use. The last page asks for consent from carers and children to be contacted again, for their school to be contacted, personal and school contact details.

Where consent is given, schools are sent a teacher’s questionnaire (TQ) and an information letter. They are not informed about treatment allocation. The TQ includes the CGI, SNAP, and questions about school-specific resource use, attendance, disruption and exclusion. Schools which do not want to participate are not contacted again.

Control group participants are not informed that they have not been selected for a treatment but continue to be sent questionnaires at the same time intervals as treatment groups. CQs and TQs are sent out every 6 months to all cohort participants. Those refusing the offer of treatment are still asked to complete outcome measures as usual every 6 months and considered members of the offer group.

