### Outcomes

#### Patient-centred outcomes

The primary outcome measured is ADHD symptomatology measured using CGI, consisting of a 10-item total score and two sub-scores measuring restlessness/impulsivity (7 items) and emotional lability (3 items). The outcome is reported by carers (unblinded) and teachers (blinded), and each intervention is compared to usual care. Secondary outcomes are carer proxy health-related quality of life (CHU-9) and sleep. Resource use is collected by asking about medication use; further ADHD interventions being used; hospital, GP, social worker and police attendances; levels of absenteeism, exclusion and criminality; and teaching assistant and other help in school.

Resource use data is collected to enable an economic evaluation alongside a clinical trial. Evaluation will include health-related quality of life assessment, with utility measures based on the CHU-9D, the cost of consultations, medications, remedies, supplements and room hire, to enable QALY and ICER calculation. The time horizon is 1 year, during which time resource use will be collected from therapists, who complete therapist forms at each consultation documenting the time spent, the venue, medications or supplements given.

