#### Statistical analysis

Statistical testing is exploratory since the study is not powered to detect statistical differences. It will be used to ensure that a difference can be seen from the interventions to proceed to the full trial, to inform sample size calculation, and to pilot test the statistical analyses selected. Analysis will focus on confidence interval estimation rather than hypothesis testing. IBM SPSS 21 statistical software [56] will be used. All statistical exploratory tests will be two-tailed with significance level (alpha) set to 5%, and 95% confidence intervals presented. Outcomes will be measured by parents and teachers at baseline, 6 months and 1 year. Both interventions tested will be compared with treatment as usual with parent and teacher measurements reported.

Missing data: post hoc tests will be performed to identify any differences between groups regarding whether data is missing completely at random or not at random. 6-month missing data will be imputed using Last Observation Carried Forward or mean substitution (for baseline data) according to tool developer recommendations [47].

‘Intention to Treat’ (ITT) analysis is used whereby participants offered treatment remain within the treatment group regardless of whether they take up the offer of treatment. The method used for statistical analysis of the outcome data will be regression analysis, with outcome change score as the dependent variable and group (homoeopathic treatment or nutritional therapy, analysed separately) as the independent variable. Analysis will control for the effects of gender, ADHD severity (CGI baseline score) and age.

The acceptability of the offer of treatment will be reported by presenting numbers for all patients offered treatment. Statistical tests will be carried out to identify characteristics of those who did and did not accept and receive treatment. Sub group analysis will explore the effect of treatment on those accessing that treatment, those taking/not taking ADHD medication and those with co-occurring autism.

The clinical effect of treatment will be explored by calculating standardised mean differences [57] for those offered and taking up the offer of each treatment to obtain sample size estimates.

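### Mean-filled teacher baselines put an error into change scores that distorts the pilot's SDs and SMDs for the full trial, though it does not bias the treatment contrast

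*Protocol article*

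**What the plan says.** The missing-data paragraph of the Statistical analysis section reads: "6-month missing data will be imputed using Last Observation Carried Forward or mean substitution (for baseline data) according to tool developer recommendations". It does not say whether the mean replaces single unanswered items or a whole absent score, nor which mean (item, scale, arm or overall) is used.

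The regression described next is fitted "with outcome change score as the dependent variable and group (homoeopathic treatment or nutritional therapy, analysed separately) as the independent variable". On covariates it says: "Analysis will control for the effects of gender, ADHD severity (CGI baseline score) and age". It does not say whether the carer's or the teacher's baseline CGI is meant. Table 2 names the analysis as ANCOVA.

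On the primary outcome, the Patient-centred outcomes section says: "The outcome is reported by carers (unblinded) and teachers (blinded), and each intervention is compared to usual care". A carer CGI is required for trial entry (Inclusion/exclusion criteria) and a Conners severity score is used for stratification (Randomisation), so the carer baseline will be present. The teacher's form depends on permission and on a willing school (Outcome measurement): "Where consent is given, schools are sent a teacher’s questionnaire (TQ) and an information letter". Forms go out again every 6 months, so a first teacher return at 6 months is possible.

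The pilot's arm size was chosen "in order to estimate the pooled standard deviation of the outcome with a reasonable degree of precision for the full trial" (Sample size). The full-trial sample size is to be based on the SMD found in the pilot, and Table 2 makes an SMD of 0.3 on the CGI a criterion for continuing.

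**The concern.** A baseline that serves only as a covariate can reasonably be filled with a mean. A baseline that is subtracted to form the outcome is a different matter, because whatever is wrong with the filled value passes directly into the change score. The child's stable difference from other children then appears as improvement or deterioration.

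The exposed measure is the teacher CGI, the only blinded report of the primary outcome. What is at stake is the variability estimate that the pilot is meant to supply. If filled baselines enter the SD of change or the SD of baseline scores, an SMD scaled by that SD is wrong too, and this carries into the full-trial sample size and the comparison with 0.3.

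**Working it through.** **Inputs from the protocol article.** Mean substitution for baseline data; change score as outcome; baseline CGI as covariate; SMD 0.4 leading to about 100 per group at two-sided alpha 0.05 and 80% power; 40% attrition leading to 166 per group; continuation SMD 0.3; 30 per arm in the pilot.

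**Assumptions not in the article.** A whole missing teacher baseline is filled with the overall mean; a share m = 20% of teacher baselines is missing completely at random; SD s is equal at baseline and 6 months; the baseline-to-6-month correlation r is 0.4 to 0.8.

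**1. The plan's own figure.** n per group = 2 × (1.960 + 0.842)² / 0.4² = 98.1, or 99 with the usual small-sample correction, against about 100 stated. 100 / 0.6 = 166.7, against 166 stated. Both reproduce, apart from rounding down.

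**2. Error for one child.** With baseline B, 6-month score Y and filled mean M:

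(Y − M) − (Y − B) = B − M.

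With an assumed mean of 75, a child at 85 on both occasions is recorded as +10 (worse) and a child at 65 on both occasions as −10 (better). Neither changed.

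**3. Treatment contrast.** Write B* for the baseline after filling and G for group. The model

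Y − B* = a + bG + cB* + error

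is the same as

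Y = a + bG + (c + 1)B* + error.

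The estimate of b is identical, so the error cancels when the same filled teacher baseline is the covariate. In simulation (30 per arm, assumed true difference −4, assumed SD 10, 10% to 50% missing) the two estimates agreed to about 1.6e-12. The mean estimate was −3.93 to −4.11, whether baselines were missing at random or more often when high. With the carer baseline as covariate the error does not cancel, but the mean estimate was still −3.92 to −4.11.

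**4. SD of change.** A true change has variance 2s²(1 − r). A change from a filled baseline has variance s². The ratio of the mixed variance to the true variance is

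[m + (1 − m) × 2(1 − r)] / [2(1 − r)].

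The last two columns take a true change-scale SMD of 0.30, and a full-trial n of 100 scaled by the variance ratio.

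| r | Variance ratio (m = 0.2) | SD ratio | SMD of 0.30 reads | n of 100 becomes |
|---|---|---|---|---|
| 0.4 | 1.16/1.2 = 0.967 | 0.983 | 0.305 | 97 |
| 0.5 | 1.00/1.0 = 1.000 | 1.000 | 0.300 | 100 |
| 0.6 | 0.84/0.8 = 1.050 | 1.025 | 0.293 | 105 |
| 0.7 | 0.68/0.6 = 1.133 | 1.065 | 0.282 | 113 |
| 0.8 | 0.52/0.4 = 1.300 | 1.140 | 0.263 | 130 |

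**5. SD of baseline.** Filled values add no spread, so the ratio is √(1 − m) = √0.8 = 0.894, about 11% too small. An SMD standardised by it would read 0.30/0.894 = 0.335, and n would be 0.8 times what is needed (80 for 100).

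**6. SD of observed 6-month scores.** No baseline enters it, so this standardiser is unaffected.

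**The case against.** **The rule may concern single items only.** It is tied to the tool developer's recommendations, which are not at hand, and Table 2 and the Feasibility outcomes section speak of missing items. Under that reading the error is much smaller. This stands as a real ambiguity. The sentence still points more naturally to whole scores: it pairs mean substitution with LOCF and confines it to baseline, the one visit with nothing earlier to carry forward, whereas unanswered items would need filling at 6 months too.

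**The regression already controls for baseline CGI.** This stands in full. A reader might infer from the 10-point errors that the estimated treatment effect is biased. The article does not support that: baseline precedes randomisation, teachers are not told the allocation, and the algebra in step 3 removes the error when the teacher baseline is the covariate.

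**A reader might also infer a precision penalty from the imputation if the carer CGI is the covariate.** In simulated trials of 30 per arm (assumed carer-teacher correlation 0.4, 20% of teacher baselines missing), the standard error in SD units of a carer-adjusted change analysis is 0.261. An ANCOVA that also contains the teacher baseline gives 0.238 (r = 0.5). At r = 0.7 the figures are 0.212 and 0.203. With no baselines missing the gap is at least as large: 0.253 against 0.226, and 0.200 against 0.189. The gap reflects the choice of covariate, not the filling of baselines.

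**The SMD's standardiser is not spelled out.** This also stands. The article refers to the SD of the outcome and gives the SMD method only by citation. If the observed 6-month SD is used, the distortion in steps 4 and 5 does not arise in the standardiser.

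**Conclusion.** The point holds in a limited form. If a whole missing teacher baseline is filled with the mean, the individual change score is wrong by the child's baseline minus that mean. The group comparison stays unbiased.

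What remains is distortion of two SDs and of any SMD standardised by them. The direction depends on the standardiser. With the SD of change, the SMD is too small when r exceeds 0.5 and too large when r is below 0.5. With the baseline SD, it is always too large. At the assumed 20% missing, a true change-scale SMD of 0.30 could fall just short of the continuation threshold (0.293 to 0.263 for r of 0.6 to 0.8), and the full-trial n could be 5% to 30% too large. These sizes rest on assumed missingness and correlations and on the whole-score reading.

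Testing in this pilot is declared exploratory, so this is a minor-to-moderate point. It is still worth settling, because informing the full-trial sample size is one of the pilot's stated purposes.

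**What to change.** In the missing-data and regression paragraphs:

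1. State that no change score is formed from an imputed whole-scale baseline.
2. Analyse the observed 6-month (and 1-year) CGI by ANCOVA, with the same reporter's baseline CGI as covariate. A mean-filled baseline is acceptable there, as a covariate only.
3. Compute the SD and SMD for the full trial, and for the 0.3 criterion, from observed scores only, and name the standardiser.
4. Limit mean substitution otherwise to single missing items within a returned questionnaire.

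This is a change of wording that needs no new data and agrees with the ANCOVA already named in Table 2. The cost is a slightly smaller number of children behind the descriptive SD and SMD.

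### Last observation carried forward enters every unreturned 6-month questionnaire as exactly zero change, which biases the intention-to-treat effect that feeds the full trial

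*Protocol article*

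**What the plan says.** All of this is in the protocol article.

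- **Imputation rule** (Statistical analysis): "6-month missing data will be imputed using Last Observation Carried Forward or mean substitution (for baseline data", a rule that the same sentence attributes to the tool developer's recommendations. No alternative or sensitivity analysis is named, and the rule does not depend on the result of the planned missingness tests.
- **Outcome analysed** (Statistical analysis): regression "with outcome change score as the dependent variable", by offer of treatment. "Analysis will control for the effects of gender, ADHD severity (CGI baseline score) and age".
- **Assessment times** (Statistical analysis): "Outcomes will be measured by parents and teachers at baseline, 6 months and 1 year".
- **Use of the results** (Sample size): the pilot is sized "in order to estimate the pooled standard deviation of the outcome with a reasonable degree of precision for the full trial", and full-trial size is to be calculated from the SMD that the pilot obtains.
- **Extent of missing data**: Sample size expects 20% attrition. Table 2 accepts a 6-month return as low as 30%. The text after Table 2 warns that dropout may be high.
- **Entry criterion** (Inclusion/exclusion criteria): the trial requires "a carer-reported CGI score of at least 65".

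**The concern.** Nothing is measured between baseline and 6 months, so the value carried forward is the baseline value. Follow-up minus baseline is then zero by construction, and the regression treats that zero as an observed outcome.

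Zero is a strong assumption in this population. Children enter on a high carer score, so some fall is expected in every arm through regression to the mean alone. Return may also differ by arm: offered families meet a therapist, while controls only receive questionnaires. If one arm has more artificial zeros, part of the shared improvement appears as a difference between arms.

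What is at stake is the pilot's main quantitative output: the offer-versus-usual-care difference, its confidence interval, and the SMD carried into the full-trial sample size.

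**Working it through.** **1. The plan's own figure.** For SMD 0.4, two-sided 5% and 80% power, n per group = 2(1.960 + 0.842)² / 0.4² = 15.70 / 0.16 = 98.1, so 99 (stated: about 100). With 40% loss, 100 / 0.6 = 166.7, so 167 (stated: 166). Both reproduce. The calculation depends directly on the SMD, so a biased SMD passes straight into it.

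**2. Inputs.** From the article: change-score outcome, baseline CGI as covariate, at least 30 per arm, 20% attrition, minimum return 30%. Assumed, because the article gives no values: SD 10 T points at each time, baseline to follow-up correlation 0.6, control improvement 3 points, true effect 4 points, missingness by arm, and loss completely at random. Improvement is written as positive.

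**3. Effect of the zeros on the mean.** If returners improve by μ on average and a fraction m is set to zero, the arm mean becomes (1 − m)μ. With equal m, the difference becomes (1 − m)(μT − μC): multiplied by 0.8, 0.6 and 0.3 at m = 20%, 40% and 70%.

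| Missing, offer / control | True difference | By formula | Simulated, carried forward | Simulated, observed only |
|---|---|---|---|---|
| 20% / 20% | 4 | 0.8×7 − 0.8×3 = 3.2 | 3.21 | 4.01 |
| 40% / 20% | 4 | 0.6×7 − 0.8×3 = 1.8 | 1.78 | 3.99 |
| 20% / 40%, both arms improve 5 | 0 | 0.8×5 − 0.6×5 = 1.0 | 1.03 | not quoted |

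The errors can also cancel. With improvements of 0.8 and 0.4 SD and 20% / 40% missing, 0.8×0.8 − 0.6×0.4 = 0.40 SD, which is the true difference. The direction therefore cannot be known in advance.

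**4. Effect on the SD.** Change-score variance becomes (1 − m)s² + m(1 − m)μ², with s² = 2×100×(1 − 0.6) = 80, so s = 8.94. At m = 0.2:

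- control: 64 + 0.16×9 = 65.44
- offer: 64 + 0.16×49 = 71.84
- pooled SD: √68.64 = 8.28, against 8.94 (simulated 8.23 v 8.87)

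The change SD would rise rather than fall only if mean change exceeded s/√(1 − m), or 1.12 s at m = 0.2.

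For the 6-month score itself, variance is 100 + 0.16×9 = 101.44 in control and 100 + 0.16×49 = 107.84 in the offer arm. The pooled SD is √104.64 = 10.23, against 10 (simulated 10.18 v 9.92). It rises slightly.

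The SMD falls with either standardiser: 3.2/8.28 = 0.39 against 4/8.94 = 0.45 on the change SD, or 3.2/10.23 = 0.31 against 4/10 = 0.40 on the score SD.

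**5. Confidence intervals.** At 20%/20% with a true effect of 4, coverage of the 95% interval was 0.93, against 0.946 for observed data. At 40%/20% it was 0.784. With baseline truncated at 65, equal missingness and no true effect, it was 0.948 (20%) and 0.946 (40%). The average standard error at 20%/20% was 1.98 and the actual sampling SD of the estimate was 2.00, so the standard error is correct for this estimator. The shortfall comes from the bias.

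**6. Sensitivity.** Truncating baseline at 65 gave 3.18 and coverage 0.928 at 20%/20%. With 37 per arm, so that about 30 return, the estimate was 3.20.

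**The case against.** The strongest objection is scope. The sentence refers to the tool developer's recommendations, and a scoring manual may deal only with items left blank on a returned form. The article discusses missing items elsewhere (Table 2 and the text on acceptability of measures), and the cited source is not at hand. This stands as a real ambiguity. However, the sentence speaks of 6-month missing data without restriction, and carrying an observation forward is a natural description of filling an absent assessment. If items alone were meant, the article has to say so.

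Second, testing is labelled exploratory and piloting the analyses is one of the aims. That reduces the weight of p-values. It does not protect an SMD that is to be used in a sample size calculation.

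Third, the inputs are assumed. The further 20% in Sample size is ineligibility or refusal, not loss to follow-up, and refusers are still sent questionnaires, so 40% missing in one arm is illustrative. Also, 140 × 0.8 × 0.8 = 89.6, so 30 per arm may already be net of attrition. The attenuation factor (1 − m) does not depend on n.

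A reader might infer more than the document supports:

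- **That the SD the pilot is sized to estimate must shrink.** Sample size refers to the SD of the outcome, not of change. Only the change SD falls.
- **That the intervals are wrongly narrow as a separate fault.** The standard error matches the sampling variability. Under-coverage follows the bias.
- **That the chance of wrongly passing the 0.3 criterion can be read off these figures.** Table 2 applies that criterion to those implementing the therapies, not to the intention-to-treat contrast.
- **That the full trial would be too large by one definite percentage.** The article does not say which SD standardises the SMD.
- **That the planned missingness tests are impossible.** The text asks "whether data is missing completely at random or not at random", and observed data can give evidence against missing completely at random.

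**Conclusion.** The point holds. As written, the rule turns each unreturned 6-month questionnaire into a change of exactly zero. With equal loss this shrinks the intention-to-treat difference by the missing fraction: 20% at the article's expected attrition, and 70% at the lowest return Table 2 would accept. With unequal loss the bias has no fixed sign. Under the stated assumptions a true 4-point effect is estimated as 1.8 at 40%/20% missing, and a null effect as about 1 point of benefit at 20%/40% with a 5-point shared improvement. The rule therefore cannot be defended as conservative. Coverage falls to about 0.93 at 20%/20% and 0.78 at 40%/20%.

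The zero-change mechanism and the (1 − m) factor follow from the article's own rules, provided the imputation covers whole questionnaires and returners represent non-returners. The figures in T points rest on assumed values for SD, correlation, shared improvement and missingness by arm. There is no bias if non-returners truly did not change, or if the errors cancel between arms, but the plan gives no reason to expect either.

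**What to change.** - State that the tool developer's substitution rule applies only to missing items within a returned questionnaire.
- For unreturned questionnaires, make the primary intention-to-treat analysis a baseline-adjusted analysis of the observed CGI values: a likelihood-based repeated-measures model over 6 months and 1 year, or multiple imputation carried out separately by arm.
- Take the SD and SMD for the full-trial calculation from observed values, and say whether the SD is that of the score or of the change.
- Keep last observation carried forward at most as a sensitivity analysis.

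The cost is a change of analysis wording, a little more programming and somewhat wider intervals. In the 20%/20% example, the standard error from observed data is 2.32 rather than 1.98. No extra data collection is needed. The replacement methods still assume that loss is explained by the observed data.

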### Randomisation

After recruitment to the STAR cohort, a three-armed internal pilot trial is subsequently conducted whereby random selections of eligible children are offered either adjunctive treatment by homoeopaths (arm 1) or nutritional therapists (arm 2). Randomisation is computer generated by an independent statistician from the University of Sheffield and held in the locked drawer of a different statistician from the University of Sheffield. Stratifying factors are age (primary 5–11/secondary 12–18), medication status (yes/no) and ADHD severity (Conners global ADHD *T* score 80+/under 80) [47]. Participants fulfilling inclusion and exclusion criteria who consent to be contacted again are identified on recruitment to the cohort. Stratifying factors are extracted and emailed to the statistician holding the randomisation list, who randomly assigns them to one of the three groups and gives them a randomly generated three-digit code by which they are subsequently identified.

Carer and child’s consent to try treatments is sought at this stage. They are sent a letter of invitation for 1 year of treatment, which includes a statement that participants can withdraw at any time; a brief description of the treatment; requests the carer to ask their child if they are happy to participate; a consent form to treatment to be signed by carer and child and returned in a pre-paid envelope; and an email address and telephone number as an alternate means of contact. The PI then rings the participants up and asks if they have any questions; if they wish to participate (if their form has not yet been returned); and if they both consent, to their details being passed on to the therapist. In the absence of a returned ‘consent to treatment’ form, carer and child’s wish to participate on the telephone is taken as verbal consent. Consent forms are then signed at the first appointment with the therapist, who further explains what treatment will constitute, as befits usual practice. Appropriate marks by young children are taken as signatures. Those children not selected act as a treatment as usual control (arm 3).

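### The outcome regression leaves out medication status, a stratification factor, and has no own-baseline term for CHU-9, sleep and possibly teacher-rated CGI

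*Protocol article*

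**What the plan says.** Protocol article, Randomisation: "Stratifying factors are age (primary 5–11/secondary 12–18), medication status (yes/no) and ADHD severity", the last being split at a Conners global T score of 80.

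Protocol article, Statistical analysis: the method for the outcome data is "regression analysis, with outcome change score as the dependent variable and group (homoeopathic treatment or nutritional therapy, analysed separately) as the independent variable". The covariates follow in one sentence: "Analysis will control for the effects of gender, ADHD severity (CGI baseline score) and age". Medication appears in that section only as a planned subgroup.

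Protocol article, Patient-centred outcomes: "The primary outcome measured is ADHD symptomatology measured using CGI", and "The outcome is reported by carers (unblinded) and teachers (blinded), and each intervention is compared to usual care". Then: "Secondary outcomes are carer proxy health-related quality of life (CHU-9) and sleep".

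Two other places bear on the point. Table 2 names the analysis as ANCOVA, with meeting its assumptions as the criterion. The Statistical analysis section calls testing exploratory, gives interval estimates priority over tests, and makes trying out the chosen analyses one purpose of the pilot.

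**The concern.** The covariate list does not match the randomisation. Age and severity carry over into the model, medication status does not, and gender, which is not a stratifier, is added. Stratifying on a prognostic factor reduces the real variability of the treatment difference. A model that ignores the factor leaves its contribution in the residual, so the printed standard error does not show that gain.

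The second issue is the baseline term. A regression of change on group gives the same treatment estimate as ANCOVA on the follow-up value only when the outcome's own baseline is in the model. One sentence covers all outcome data, and the only baseline it names is CGI. For CHU-9 and sleep, the Statistical analysis section and the ANCOVA label in Table 2 therefore describe different analyses.

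What is at stake is the width of the intervals, which are the pilot's main statistical output, and whether the model is fit to carry into the full trial.

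**Working it through.** **The plan's own figure.** Full-trial size for SMD 0.4, two-sided alpha 0.05 and power 80%: 2 × (1.96 + 0.84)² / 0.4² ≈ 98.1, so 99 per group (99.1 with the t distribution), against about 100 stated. With 40% attrition, 100 / 0.6 = 166.7, against 166 stated. Both reproduce, and neither depends on the covariate list.

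**Medication status.** From the protocol: at least 30 per arm; 2 × 2 × 2 = 8 strata; each intervention compared with usual care in a separate model containing group, gender, baseline CGI and age. Assumed, because the article gives no figures: permuted blocks of 3 within strata, half the children medicated, and medication explaining 0–30% of residual variance. With no treatment effect and 5,000 simulated trials per setting, at 30 per arm:

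| Share of variance | True SD of estimate | Mean reported SE | SE / SD | Type I error | Type I error with medication added |
|---|---|---|---|---|---|
| 0% | 0.2638 | 0.2607 | 0.99 | 5.2% | 5.2% |
| 5% | 0.2587 | 0.2613 | 1.01 | 4.3% | 5.3% |
| 10% | 0.2501 | 0.2609 | 1.04 | 4.1% | 5.1% |
| 20% | 0.2393 | 0.2621 | 1.10 | 3.0% | 5.1% |
| 30% | 0.2221 | 0.2629 | 1.18 | 2.2% | 5.1% |

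Columns 2 to 5 are for the model as planned. Simulation error is about 1% on the SD (1/√10,000) and 0.3 percentage points on the type I error (√(0.05 × 0.95 / 5,000)). The large-sample approximation 1/√(1 − share) gives 1.026 at 5% and 1.054 at 10%, the same order of size.

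At 100 per arm the SE/SD ratio runs from 0.99 to 1.21, and type I error from 5.2% down to 1.7%.

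The true SD hardly moves when medication is added (0.2393 to 0.2371 at a 20% share). The omission overstates the uncertainty far more than it increases it.

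**Own baseline.** Take equal variances at the two times and a baseline–follow-up correlation ρ (assumed). In units of the outcome variance:

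- change score without own baseline: 2(1 − ρ)
- own baseline in the model: 1 − ρ²
- variance ratio: 2/(1 + ρ)

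Baseline CGI recovers a little. If it correlates r with the outcome's baseline and r₁ with its follow-up, the first variance falls by (r₁ − r)². With r from 0 to 0.5 and r₁ from rρ to r:

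| ρ | 2(1 − ρ) | 1 − ρ² | SE ratio, CGI recovers nothing | SE ratio, r = 0.5 and r₁ = rρ |
|---|---|---|---|---|
| 0.3 | 1.40 | 0.91 | 1.24 | 1.19 |
| 0.5 | 1.00 | 0.75 | 1.16 | 1.12 |
| 0.7 | 0.60 | 0.51 | 1.08 | 1.06 |

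The standard error is therefore about 6–24% larger than needed over this range. For CGI with the same rater's baseline in the model, the loss is zero.

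**Which rater.** Both carers and teachers complete the CGI. The covariate sentence does not name a rater, but it uses the severity label from the Randomisation section. There, severity is extracted as children join the cohort, and cohort entry rests on the carer-reported score. The carer's score is the natural reading, and it would leave teacher CGI, the blinded report of the primary outcome, without its own baseline.

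**The case against.** The case for leaving the text alone is that little depends on it, and much of that is right.

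- **Size.** Omitting medication matters only if medication predicts change after allowing for baseline CGI. The article gives no evidence on this, and a planned subgroup concerns effect modification, not prognosis. At a 5–10% share the effect is small.
- **Progression.** The treatment-effect criteria in Table 2 are an SMD and a T-score change. Neither turns on a p-value or an interval width.
- **Condensed text.** Covariates for each outcome are often left to a fuller document, and a matched-rater reading of the CGI covariate is open. This tempers the teacher CGI point. It does not remove the others, because the article states a specific list that lacks a stratifier and gives CGI as the only baseline for all outcome data.

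A reader might also infer more than the document supports:

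- **That the primary outcome has the wrong baseline.** It does not: for carer CGI the covariate is the outcome's own baseline.
- **That false positives rise, or the effect estimate is biased.** The omission of medication is conservative and leaves the estimate centred. A missing own baseline costs precision but does not invalidate the standard error. A chance baseline imbalance would shift a particular result, but the estimator is unbiased over randomisations.
- **That full-trial size or the QALYs are undermined.** The Sample size section uses the primary-outcome SMD, and nothing routes this regression into the QALY calculation.

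**Conclusion.** The point holds, at modest size, in two parts.

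1. The model omits one of the three stratification factors. If medication is prognostic, intervals at 30 per arm are too wide by about 1–4% (5–10% of residual variance) and up to about 18% (30%), with type I error between 4.3% and 2.2%. If it is not prognostic, there is no effect.
2. CHU-9 and sleep, and teacher CGI if the covariate is the carer's score, lack their own baseline. Their standard errors are valid but about 6–24% larger than needed for correlations of 0.7 to 0.3.

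The variance shares, block scheme, medicated proportion and correlations are assumptions. The mismatch between the covariate list and the stratification factors is plain from the text. Because testing is exploratory, no conclusion of the pilot is overturned. It is still worth correcting, since the pilot rests on interval estimates and is meant to try out the analysis for the full trial.

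**What to change.** Replace the covariate sentence with one that specifies, for each outcome and rater: change (or the follow-up value) regressed on group, the baseline value of that same outcome from the same rater, age, baseline medication status, baseline CGI as severity, and gender. State whose CGI is the severity covariate. For a CGI outcome where severity is that same rater's score, the two baseline terms are one. Table 2's ANCOVA label would then fit every outcome.

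No new data collection is called for: medication status is known at randomisation and the outcomes are measured at baseline. The cost is one sentence and one or two degrees of freedom per model.
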